### Step 3: Implementation of cervical screening strategies

Participating services will be provided a customised report with findings from co-design workshops. This will be used to clearly define the strategies chosen and outline the roles and responsibilities of the research team and the service in implementing the strategies. Support will be provided to update cervical screening data (as requested) along with direct research costs to further promote availability of self-collection and cervical screening during the pilot period, using the most appropriate methods for their community. The research team will undertake resource development, facilitate training of the workforce and other means of strengthening existing capabilities in cervical screening as determined during co-design. Services will implement the co-designed strategies for 12 months to improve delivery of cervical screening in their communities and increase service level participation. Strategies will be implemented with support from research staff tailored to local service requests.

Each participating site will co-design and implement locally tailored strategies to improve cervical screening participation among Aboriginal and Torres Strait Islander women and people with a cervix. These strategies reflect community priorities and service capacities, and were developed collaboratively between health services, community members, and the research team. Rather than being prescriptive, the strategies are designed to enhance usual clinical care and allow each service to select and adapt approaches that best suit their local context. This includes choosing from a suite of options based on identified needs, existing resources, and community preferences. The flexible design ensures that HPV self-collection is embedded into routine care sustainably. Research staff meet regularly with each participating service according to their individual needs and provide tailored support and adaptation. Examples of strategies include:

1.Community engagement strategies:a. Community awareness campaigns: Co-designed posters, brochures, and social media content developed jointly by service staff and the research team. These materials promote the choice of HPV self-collection directly to ACCHO clients.b. Health promotion: Community events and campaigns hosted by ACCHO to raise awareness of HPV self-collection, provide education, and encourage clients to participate in cervical screening.2.Participant level strategies:a. Follow-up reminders: Modification of SMS or phone call reminders for clients who are due for cervical screening with the offer of self-collection.b. Incentives: Participants who complete cervical screening (i.e., either clinician collected or self-collected sample) are offered a small incentive, such as a gift card or wellbeing pack, to acknowledge their participation and encourage uptake. Incentives are provided immediately after screening by service staff, either during consultations or at community events.3.Workforce level strategiesa. Staff education and training: Delivered by the research team, these sessions cover cervical screening guidelines, self-collection procedures, and communication strategies for ACCHO clients. Training is provided in-person or online depending on site needs.b. Clinical champions: Identified within each service to support implementation, mentor staff, and liaise with the research team.4.Health service level strategies:a. Data Audit and Cleaning: Practice staff and/or research support teams conduct detailed audits of cervical screening data within practice management software to identify eligible participants and ensure data accuracy. This process involves checking individual client records against the NCSR and manually updating local records where discrepancies are found. The aim is to create a reliable and up-to-date screening register within each service, which supports targeted outreach and follow-up, and ensures that screening invitations are based on accurate information.b. Workflow Integration: Services have integrated cervical screening checks into routine clinical workflows to promote opportunistic screening. This includes embedding prompts into appointment systems and clinical templates to ensure that cervical screening status is reviewed and self-collection is offered during regular visits, such as 715 health checks or chronic disease reviews. Staff are encouraged to offer screening as part of everyday care, supported by incentives for participants who complete cervical screening and streamlined documentation processes to reduce administrative burden and improve uptake.

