### Step 2: Co-design of strategies for implementing self-collection at each site

We will work with nominated staff at participating services to facilitate co-design workshops, set priorities collaboratively, and design locally tailored strategies, engaging community members as determined by each service. This process will follow key principles of co-design with Aboriginal and Torres Strait Islander peoples, including leadership, cultural grounding, respect, benefit to community, inclusive partnerships, transparency, evaluation, and reciprocity [40,41].

Co-design will occur through a structured yet flexible and iterative process facilitated by the research team and tailored to each site. We will begin by meeting with nominated service staff, often those involved in cervical screening or research, to agree on the preferred approach and identify who should participate, such as other clinical staff, non-clinical staff, and local community members or groups. Each site will be offered up to two in-person visits; however, workforce availability and geographic challenges may mean many engagements occur online, supplemented by virtual planning meetings and collaborative workshops.

While co-design will be guided by each service, it will broadly address local priorities and goals for cervical screening, explore context, identify barriers and facilitators, and develop strategies to enhance access. These ideas will be refined into implementation strategies through multiple interactions between the research team and service staff. This iterative approach allows strategies to evolve in response to feedback and context, ensuring each solution is tailored to the unique needs of the service. In practice, this means strategies may iteratively develop over the course of the implementation period as new priorities are identified. There will be no predetermined list of strategies; all ideas will emerge through co-design to support local needs. However, a common focus across sites will be improving data support and access. Strategies to achieve this will vary depending on local systems and capacity. All strategies will aim to increase participation of under- and never-screened women and people with a cervix in cervical screening using HPV self-collection. Strategies may include community engagement, participant-level interventions, workforce development, and system or service-level changes.

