
### Step 4: Evaluation

#### Evaluation Framework.

The evaluation of this research will be conducted within an overarching conceptual framework that combines key constructs from the RE-AIM Framework [43] with the Health Equity Implementation Framework [44]. The evaluation variables are outlined in Table 1. During the co-design process services may identify additional variables or research questions of interest to their unique context and these will be added to the evaluation framework. Quantitative data will be used to assess intervention impact, interpreted alongside an understanding of how colonial health structures shape outcomes. Indigenist qualitative methods will provide context, centring participants’ experiences, voices, and definitions of meaningful change. Evidence of “success” will be judged equally by increases in the primary outcome toward cervical screening elimination targets (i.e., 70% participation) and by the extent to which participants define the co-design and implementation phases as “successful”, including the degree to which these practices embody sovereignty and support health system (re)build.

**Table 1 pone.0336004.t001:** Evaluation variables.

Approach	Collection methods	Variables
Quantitative	• De-identified data extracted from service Record Management Software and/or Clinical Audit Tools at baseline (#T0), periodic intervals as determined by each service (approximately 3 monthly), and 12 months for pre-post analysis (#T1). Services can provide data at 3 and 6 months post implementation.	De-identified cervical screening data for screen eligible Aboriginal and Torres Strait Islander clients at each service (number and proportion): • Cervical screening participation #T0, #T1 • Under-or never-screened #T0, #T1 • Cervical screens by collection method (i.e., self- or clinician-collection) #T1 • HPV positive tests #T1
Qualitative	• Qualitative Yarns and Yarning circles with ACCHO staff and eligible clients (women and people with a cervix)	• Yarns will cover topics such as: experience of participating in or implementing strategies; perceptions of effectiveness; reach and sustainability of strategies; challenges and strengths throughout implementation period.

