### Data collection and analysis

#### Cervical screening data.

The primary outcome will be the number and proportion of Aboriginal and Torres Strait Islander women and people with a cervix who are overdue for cervical screening (under-screened) or have no recorded history of a cervical screen (never-screened) at the completion of the study, compared to the before period. Secondary outcomes are cervical screening participation, the number and proportion of cervical screens conducted by collection type (self-collect versus clinician collect) and HPV positive tests in the 2-years before and during the study period. Quantitative outcomes data will be obtained using one or a combination of the following pathways to be determined by the services’ preferences: from local practice management software, practice audit tools, from the National Cervical Screening Register (NCSR) and/or manual audit of relevant patient records. De-identified data will be provided to nominated members of the research team via secure methods.

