### Limitations

The study uses cervical screening data from available sources, including practice management software. This presents several limitations as screening records within these platforms can contain inconsistencies and incomplete fields. To mitigate this, strategies focusing on data audits and cleaning will be prioritised (where feasible). Where this is not possible, we will explicitly acknowledge the resulting uncertainty. Missingness will be assessed descriptively to characterise data quality, but no formal imputation will be undertaken consistent with the study’s implementation focus.

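### At services that audit records against the NCSR after the baseline extract, T0 and T1 rest on different records, so the primary outcome can improve without new screening

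*Protocol article*

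**What the plan says.** - **Outcome.** Under Cervical screening data, the primary outcome counts clients who are overdue or who "have no recorded history of a cervical screen (never-screened) at the completion of the study, compared to the before period". The Analysis section divides this by the number of screen-eligible clients. Participation, a secondary outcome, is a recorded screen within five years over the same denominator.
- **Timing and source.** Table 1 describes "De-identified data extracted from service Record Management Software and/or Clinical Audit Tools at baseline (#T0") and again at 12 months (T1). For the source, the Cervical screening data section states "Quantitative outcomes data will be obtained using one or a combination of the following pathways to be determined by" each service's preference. It lists local software, audit tools, the NCSR and manual audit.
- **Quality of local records.** The Introduction describes local software as incomplete and inconsistently linked to the NCSR.
- **Intervention.** Strategy 4a in Step 3 is a data audit: "This process involves checking individual client records against the NCSR and manually updating local records where discrepancies are found". Step 2 adds "However, a common focus across sites will be improving data support and access". Step 3 makes the help optional: "Support will be provided to update cervical screening data (as requested").
- **Limitations.** Cleaning appears only as a remedy for poor records: "To mitigate this, strategies focusing on data audits and cleaning will be prioritised (where feasible").

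**The concern.** The outcome is a property of the record, and one of the strategies changes the record between the two measurements. A client screened elsewhere before T0, whose test never reached the local system, counts as under- or never-screened at T0. If the audit then enters that test and it is still current, she counts as screened at T1, although nobody screened her during the study.

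Cleaning one side of the comparison turns an error common to both periods into one that differs by period, in the direction of success. The planned multi-level logistic model cannot remove it: at an audited service the correction coincides with the period effect, and there is no control group. Corrected records also persist, so the 3- and 6-month retention data would carry the same artefact. Success is judged partly on movement towards 70% participation, and the results are meant to inform national scale-up, so a mixture of new screening and newly found screening would mislead.

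**Working it through.** **The plan's own figure.** For 20% against 40%, two-sided 5% and 80% power, the sample size with continuity correction is 91 per arm (82 without). The design effect is 1 + (50 − 1) × 0.1 = 5.9. The total is 2 × 91 × 5.9 = 1073.8, so 1074; 12 × 50 × 2 = 1200. The sample size reproduces, and the point does not rest on an arithmetic slip.

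**Inputs.**
- U0, share recorded as under- or never-screened at T0: 50% (Sample size section, about half or more), or 58% (100% − 42% recorded as screened, Introduction).
- Assumed transition from under-screened to screened in 12 months: 20% at baseline, 40% targeted (Sample size section).
- m, share of those clients who hold a current test missing from the local record: **not in the documents; assumed 5% to 30%**.
- c, share of records audited after T0: not in the documents; shown for 1 and 0.5.

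**Formulas.** With no change in true screening status, U1 = U0 × (1 − m × c). On the planning scale with c = 1, and ordinary screening continuing at 20% among the clients who are truly under-screened, apparent transition = m + (1 − m) × 0.20.

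| m | U1 from 50%, c = 1 | U1 from 50%, c = 0.5 | U1 from 58%, c = 1 | Apparent transition, c = 1 |
|---|---|---|---|---|
| 5% | 47.5% | 48.75% | 55.1% | 24% |
| 10% | 45% | 47.5% | 52.2% | 28% |
| 20% | 40% | 45% | 46.4% | 36% |
| 25% | 37.5% | 43.75% | 43.5% | 40% |
| 30% | 35% | 42.5% | 40.6% | 44% |

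**Value of m that mimics the planned effect.** Solve m + (1 − m) × 0.20 = 0.40: m = (0.40 − 0.20) / 0.80 = 0.25.

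**Which found tests count.** The numerator pools overdue and never-screened clients. A found test that still leaves the client overdue moves her from never-screened to under-screened and leaves the primary outcome unchanged. Only tests that make her up to date enter m.

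**After the repair.** If T0 status is derived from the reconciled record by test date, a test dated before T0 counts at both time points, and the artefact in this calculation is zero for any m.

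**The case against.** A reader might infer that every T0 figure is uncorrected and every T1 figure corrected. The documents do not support that. The audit is one example among strategies that each service chooses, it is supported on request and where feasible, and no section dates it relative to the T0 extract. A service that uses the NCSR or a manual audit for both periods would avoid the problem. The point therefore holds only for services that audit after T0 and leave T0 as it was.

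A reader might also infer that a 20% correction share reproduces the planned effect, since 0.50 × 0.20 = 10 points and 0.50 × (0.40 − 0.20) = 10 points. That ignores that ordinary screening then acts only on the remaining 80%. On the protocol's own scale 20% gives 36%, and it takes 25% with every record audited.

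The text also leaves room for classification by test date, since participation has a five-year look-back and the model accounts for clients present in both periods. The exact rule could sit in an analysis plan not shown here. But an extract taken at baseline holds only tests entered by then, and the look-back cannot recover the rest. The Limitations section moreover presents the cause of the bias purely as a remedy.

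Other parts of the objection stand. Audits may remove wrong entries or change the denominator. The implementation worksheet (Process data) should identify which services audited and when. The protocol already promises cautious interpretation of modelled findings. These bear on size and reach, not on the mechanism.

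**Conclusion.** The concern holds in conditional form. Where a service reconciles its records with the NCSR after its T0 extract, and T0 is not reclassified, the primary comparison and five-year participation are biased towards success. The protocol requires neither reclassification nor one source at both time points, and it does not name the bias.

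The size cannot be given, because no discrepancy rate is reported. Under the assumed range with full audit, the spurious fall from a 50% baseline is 2.5 to 15 points, and half that if half the records are audited. About 25% of apparently under-screened clients holding a current unrecorded test, with full audit, would match the whole planned effect. The documents do not show that any of these values applies. The matter should be settled before the T1 data are classified, because new and newly found screening cannot be told apart if T0 is kept only as first extracted.

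**What to change.** - For the primary and participation outcomes, classify T0 status at each service from the same reconciled record used for T1, counting all tests dated on or before T0, whenever they were entered.
- Use one data pathway per service for both time points.
- Where an audit was done, repeat the NCSR check up to the T1 date. Otherwise tests done elsewhere after a mid-period audit are missed at T1 while T0 is complete, which would bias against the strategies.
- Report the original T0 extract descriptively and label its difference from the reclassified T0 as the data-cleaning effect.
- Show audited and non-audited services separately.
- Revise the Limitations section to name this bias.

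**Cost.** The service-side extract must be re-run, and the NCSR check repeated at audited services. Services can apply the date rule themselves and still supply de-identified data; if research staff help with client-level records, the further ethics approval mentioned in Step 1 applies. Clients who left before the audit remain unreconciled and must be shown separately. The audit strategy itself need not change.

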
### Step 4: Evaluation

#### Evaluation Framework.

The evaluation of this research will be conducted within an overarching conceptual framework that combines key constructs from the RE-AIM Framework [43] with the Health Equity Implementation Framework [44]. The evaluation variables are outlined in Table 1. During the co-design process services may identify additional variables or research questions of interest to their unique context and these will be added to the evaluation framework. Quantitative data will be used to assess intervention impact, interpreted alongside an understanding of how colonial health structures shape outcomes. Indigenist qualitative methods will provide context, centring participants’ experiences, voices, and definitions of meaningful change. Evidence of “success” will be judged equally by increases in the primary outcome toward cervical screening elimination targets (i.e., 70% participation) and by the extent to which participants define the co-design and implementation phases as “successful”, including the degree to which these practices embody sovereignty and support health system (re)build.

**Table 1 pone.0336004.t001:** Evaluation variables.

Approach	Collection methods	Variables
Quantitative	• De-identified data extracted from service Record Management Software and/or Clinical Audit Tools at baseline (#T0), periodic intervals as determined by each service (approximately 3 monthly), and 12 months for pre-post analysis (#T1). Services can provide data at 3 and 6 months post implementation.	De-identified cervical screening data for screen eligible Aboriginal and Torres Strait Islander clients at each service (number and proportion): • Cervical screening participation #T0, #T1 • Under-or never-screened #T0, #T1 • Cervical screens by collection method (i.e., self- or clinician-collection) #T1 • HPV positive tests #T1
Qualitative	• Qualitative Yarns and Yarning circles with ACCHO staff and eligible clients (women and people with a cervix)	• Yarns will cover topics such as: experience of participating in or implementing strategies; perceptions of effectiveness; reach and sustainability of strategies; challenges and strengths throughout implementation period.
Process	•Baseline survey completed by staff •Worksheet to complete process data •Yarns with service providers	• Service characteristics (e.g., workforce) • Number and type of strategies implemented • Costs and staff time to implement strategies • Barriers to adoption and sustainability

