Additionally, unacceptable disparities persist in cervical screening rates and outcomes for Aboriginal and Torres Strait Islander women and people with a cervix. While data by Indigenous status is not routinely available from the NCSP, localised studies consistently show that participation in cervical screening is substantially lower for Aboriginal and Torres Strait Islander women compared to other women, averaging 20 percentage points lower [15,16]. Even within Aboriginal Community Controlled Health Organisations (ACCHOs), which provide a supportive and culturally safe healthcare setting, only 42% of screen-eligible Aboriginal and Torres Strait Islander regular clients had a cervical screening test recorded in the local patient management system within the previous five years as of June 2023 [17]. However, local patient management software does not readily support ACCHOs to reliably track cervical screening participation, with incomplete data affecting national Key Performance Indicators, inconsistent integration with the National Cancer Screening Register (NCSR), and system constraints that prevent extraction of HPV self‑collection uptake at a service level.

To achieve cervical cancer elimination for all women and people with a cervix, including priority groups such as Aboriginal and Torres Strait Islander peoples, Australia must urgently address systemic failures. Significant access barriers impact the ability of Aboriginal and Torres Strait Islander women and people with a cervix to access cervical screening. Invasive clinical examinations have long been a barrier to participating in cervical screening [10,18]. Other barriers to self-collection include difficulties in identifying eligible participants, interpreting guidelines, and implementation issues limiting primary care providers ability to offer self-collection [8,19]. These barriers, combined with distrust of colonial institutions, legacies of intergenerational trauma and racism experienced within mainstream healthcare settings, necessitate concerted efforts to improve the experience of cervical screening for Aboriginal and Torres Strait Islander women and people with a cervix [5,10]. Strategies that prioritise Indigenous knowledge and strengths, without reinforcing misconceptions that fuel racism and inequity within the Australian health system, are essential.

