### Analysis

Primary and secondary outcomes will be calculated comparing data from the before (*T0*) and after (*T1*) period. Retention of effects will be measured for services who provide data at 3- and 6-month intervals in the post-implementation period. For the primary outcome, the number and proportion of all screen eligible clients at the services who are under-screened or never-screened at *T1* compared to *T0* (number of under- and never-screened screen eligible clients/number of screen eligible women). Secondary outcomes are cervical screening participation rate (number with a recorded cervical screen in the previous 5-years/number of screen eligible clients), and the number and rate of cervical screens conducted using self-collection (number of tests conducted using self-collection/number of screening tests), and the HPV positivity (number of HPV positive tests/number of screening tests). Descriptive analysis will be used to analyse cervical screening data, with regular interim reports made available to participating services. Primary and secondary outcomes will be calculated comparing data from the before (T0, > 24 months) and after (T1, 12 months) period. The before and after intervention periods will be compared descriptively, and using multi-level logistic regression models clustered on site and allowing for participants who are active in both periods. Due to the small number of participating services, modelled findings and secondary subgroup analyses will be interpreted cautiously, with emphasis on direction and magnitude. A subgroup analysis will also be conducted of the primary outcome among women who have never screened or screened >10 years ago. These will be considered exploratory with no adjustment for multiplicity planned given the implementation focus. Data will be analysed using Microsoft Excel (Microsoft Corporation) and STATA software (StataCorp, version 18).

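### Table 1 schedules collection method and HPV positivity at T1 only, although the text makes both before-and-after outcomes, and nothing holds a service's data source constant across the two periods

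*Protocol article*

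**What the plan says.** **Schedule in Table 1 (Step 4: Evaluation).** Four quantitative variables are listed. Two carry both time tags: "Cervical screening participation #T0, #T1" and "Under-or never-screened #T0, #T1". Two carry one: "Cervical screens by collection method (i.e., self- or clinician-collection) #T1" and "HPV positive tests #T1". The collection column reads "De-identified data extracted from service Record Management Software and/or Clinical Audit Tools at baseline (#T0" and goes on to roughly three-monthly extractions and a 12-month extraction tagged #T1.

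**Schedule in the text.** Cervical screening data names three secondary outcomes: participation, screens by collection type, and "HPV positive tests in the 2-years before and during the study period". Analysis states twice that "Primary and secondary outcomes will be calculated comparing data from the before" period with data from the after period. The second time, it attaches more than 24 months to T0 and 12 months to T1. It defines the self-collection share as self-collected tests over all screening tests, and HPV positivity as positive tests over all screening tests.

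**Sources.** Table 1 names service record software and clinical audit tools. Cervical screening data adds the national register and manual record audit, in any combination the service prefers. The Introduction says that local patient management software has "system constraints that prevent extraction of HPV self"-collection uptake for a service. Step 3 gives auditing and correcting local records against the register as an example strategy, and Limitations gives such work priority only where feasible.

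**The concern.** Self-collection is the practice being implemented, so its share of screens is the most direct quantitative measure of uptake. The text promises a before-and-after comparison of that share and of HPV positivity. A service or analyst working from Table 1 would extract neither at baseline.

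A second, smaller problem bears mainly on collection method. If a service supplies the before window from local software and the after window from a register check or cleaned records, the two values differ in completeness as well as in practice. Nothing in the article rules that out, and cleaning the records may itself be part of what is implemented between the two periods.

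**Working it through.** The point rests on the text rather than on a figure. The article's one calculation, in Sample size, concerns movement out of under-screening. It reproduces: 91 per arm (20% versus 40%, 80% power, two-sided 5%, with continuity correction), design effect 1 + (50 − 1) × 0.1 = 5.9, and 2 × 91 × 5.9 = 1073.8, stated as 1074. Nothing in it depends on Table 1's tags for these two variables.

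**Step 1: schedule against analysis.**

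| Outcome | Table 1 | Cervical screening data and Analysis |
|---|---|---|
| Under- or never-screened (primary) | T0, T1 | T0 versus T1 |
| Participation | T0, T1 | T0 versus T1 |
| Collection method | T1 | T0 versus T1 |
| HPV positive tests | T1 | T0 versus T1 |

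Two of the four variables, and two of the three secondary outcomes, do not match. Because the other two entries in the same cell carry both tags, the single tags look deliberate.

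**Step 2: could T1 alone be enough?** Table 1 uses the tags for extraction times. Analysis uses them for periods, with T0 the before period and T1 the after period. On the Analysis usage, a T1-only variable has no before value. On the Table 1 usage, a single 12-month extraction could count dated tests in both windows. The participation outcome already needs a recorded screen within the previous five years, so screening dates are assumed to be held. The article does not state this look-back for collection method or HPV result.

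**Step 3: source.** The Introduction's limit covers one system (local patient management software) and one item (self-collection uptake). It does not mention audit tools or HPV results. The register and manual audit are permitted. What is absent is any rule that a service uses the same pathway for both windows.

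**Step 4: direction of the possible distortion.** Let the true self-collection share be p in both periods, with a fraction a of self-collected tests labelled as such and the rest counted as clinician-collected. The recorded share is a × p, so a rise in a looks like a rise in uptake. As an assumption only: with p = 30% and a at T0 anywhere from 0.5 to 1, the recorded T0 share runs from 0.5 × 30% = 15% to 1 × 30% = 30%, against 30% at a fully labelled T1. The documents supply neither p nor a, and state no rule for unlabelled tests.

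**The case against.** The best defence is that participation and under-screening are statuses at a point in time and need two snapshots, whereas tests are dated events that one 12-month extraction can place in either window. On that view the T1 tag is merely terse. This stands in part: a reader might infer from Table 1 that the baseline is lost or that the contrast is impossible, and the documents do not support that. But the look-back is nowhere stated, and Analysis uses the same labels in a sense that conflicts with it.

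A reader might also infer that services cannot supply either outcome. That is not supported. The Introduction's statement is limited to local software and self-collection uptake, Table 1 also lists audit tools, and Cervical screening data already allows the register and manual audit. Step 2 makes better data support a common focus across sites, and Limitations undertakes to acknowledge uncertainty where cleaning is not feasible.

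Finally, nothing says that sources will switch between periods, so no particular size of spurious increase can be claimed. This is correct. The point is only that the article leaves the switch open.

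**Conclusion.** The timing contradiction holds: Table 1 and the analysis text disagree on whether two of the three secondary outcomes have a baseline. It needs correcting, but it is a matter of schedule and labelling and does not mean that data are irrecoverable. Recovery assumes that the chosen source holds a date together with the collection method or HPV result for tests in the before window.

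The source point holds in a narrower form. Free choice of pathway, the stated limit of local software, and record cleaning during implementation together leave the self-collection contrast open to a change in recording. For HPV positivity the documents show no such software limit, so the finding there rests chiefly on the missing T0 tag. The size of any distortion cannot be derived from the article; the 15% to 30% range is an assumption and measures nothing in this plan. The primary outcome and the sample size are not affected.

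**What to change.** 1. In Table 1, tag both variables #T0, #T1. Alternatively, state that dated tests in the before window are counted retrospectively at the 12-month extraction.
2. List the register and manual audit as sources in Table 1, matching Cervical screening data.
3. Leave the pathway to each service, but require the same source for both windows for these two outcomes. Making the register or manual audit compulsory would override the service-preference rule and is not needed.
4. Where a service cannot supply collection method or HPV result for both windows, report its T1 value descriptively and leave it out of the before-after contrast for that outcome.
5. While editing, align the before window, which is two years in Cervical screening data and more than 24 months in Analysis.

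The cost is wording plus some extra extraction, or a secondary contrast on fewer services. Where research staff need client-level access for cleaning or audit, Step 1 already says that additional ethics approval will be sought, so that route takes time. Register extraction may also take effort, since the Introduction notes that program data by Indigenous status are not routinely available. Data collection is expected to run to 30 September 2026, and the before window can be extracted retrospectively where the chosen source holds the fields.
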